#### Exclusion criteria

Patients with any of the following conditions (Table 2) will be excluded: non-natural menopause, due to surgery (for example, hysterectomy with ovarian conservation, and hysterectomy with bilateral oophorectomy; because the severity or patterns of symptoms may differ from the natural menopause, we therefore exclude these participants [22,23]), radiation, or medication; use of HRT, selective serotonin reuptake inhibitors, vitamin E or black cohosh (which was reported may alleviate menopausal symptoms [24]) in the past 4 weeks; any contraindication of HRT (for example, family history of breast cancer, hysteromyoma, benign galactophore diseases, or ovarian cyst); unknown causes of vaginal hemorrhage; poorly controlled hypertension, diabetes mellitus; history of malignant cancer, mental disorders (including depression), thyroid diseases, diabetic neuropathy; dermatosis (for example, eczema, psoriasis); any serious diseases of the heart, liver, or kidney (there may be risks that acupuncture induces stress action and thus harms patients with serious illness); coagulation defeats or use of anticoagulant medicine (for example, warfarin, heparin, and so forth – the acupuncture procedure involves penetration of the skin, we therefore will exclude participants with bleeding problems); use of sedative or anti-anxiety drugs; cigarette smoking, alcohol or drug abuse; artificial joints or heart pacemaker; pregnant women or women in lactation (it is still unclear whether acupuncture will lead to abortion or other side effects); and participation in other clinical trials.

#### Recruitment procedures

Three strategies will be used to recruit participants with perimenopausal syndrome. The first is to recruit participants in outpatient clinics from the three hospitals. The chief physicians from the departments of gynecology and acupuncture in each hospital were invited to attend a discussion of how to recruit patients. Research assistants will be sent to their departments to help screening participants. Moreover, posters of this trial will be shown outside the clinics to attract possible candidates. Second, we will post advertisements through television broadcasts, newspapers, and so on. In these advertisements, we will briefly introduce the population we want to include, and mention the free treatment for participants who are eligible. Third, we will organize several education groups for women experiencing the perimenopausal period; introducing these people to some basic knowledge and healthcare, as well as this trial in order to attract possible patients who want to participate.

### Interventions and comparison

#### Rationale for acupuncture and auricular acupressure protocol

The acupuncture plus auricular acupressure protocol in this trial was formed in two steps: first, we screen for a range of acupuncture points, auricular points, and stimulation methods through a systematic review of record on ancient books and acupuncture textbooks, as well as results of published articles [25]. Second, meetings were held to further screen for a standardized acupuncture protocol and consensus reached among acupuncture experts in China. Based on the theory of acupuncture and TCM, perimenopausal syndrome is caused by kidney deficiency, exhaustion of *Tiangui* (sex promoters), deficiency of essence and blood, depletion of the Chong and Ren meridians, imbalance between Yin and Yang of the kidney, and dysfunction of the viscera. According to TCM differentiation, perimenopausal syndrome corresponds to the main pattern of kidney Yin deficiency, kidney Yang deficiency, kidney Yin and Yang deficiency, liver and kidney deficiency, disharmony between heart and kidney, and spleen and kidney Yang deficiency [26,27]. We therefore chose Guanyuan (RN4), Zigong (EX-CA1), Zusanli (ST36), and Sanyinjiao (SP6) as the primary acupuncture points. In addition, subsidiary acupoints based on the different symptoms of each patient are Hegu (LI4) and Fuliu (KI7) for hot flashes and sweats; Baihui (DU20) and Anmian for sleep disorders; Taichong (LR3) and Shenmen (HT7) for mood disorders; Fengchi (GB20) and Tinggong (SI19) for dizziness and tinnitus; Ligou (LR5) and Taixi (KI3) for vaginal dryness and painful intercourse; and Xuanzhong (GB39) and Yanglingquan (GB34) for aching bones. All of the acupoints chosen above, except Guanyuan (RN4) and Baihui (DU20), which are located in the middle of line, are needled bilaterally. According to the theory of TCM, we also choose auricular points as follows: heart (CO_15_), liver (CO_12_), kidney (C0_10_), spleen (CO_13_), endocrine (CO_18_), internal genital (TF_2_), subcortex (AT_4_), Er Shenmen (TF_4_), sympathetic (AH_6a_), and apex of antitragus (AT_1, 2, 4i_) (Table 3).

**Table 3 T3:** Acupuncture points and auricular points

**Point**	**Primary**	**Additional**
Acupuncture	Guanyuan (RN4)	Hegu (LI4), Fuliu (KI7)
	Zigong (EX-CA1)	Baihui (DU20), Anmian
	Zusanli (ST36)	Taichong (LR3), Shenmen(HT7)
	Sanyinjiao (SP6)	Fengchi (GB20), Tinggong (SI19)
		Ligou (LR5), Taixi (KI3)
		Xuanzhong (GB39), Yanglingquan (GB34)
Auricular	Heart (CO_15_)	
	Liver (CO_12_)	
	Kidney (C0_10_)	
	Spleen (CO_13_)	
	Endocrine (CO_18_)	
	Internal genital (TF_2_)	
	Subcortex (AT_4_)	
	Er Shenmen (TF_4_)	
	Sympathetic (AH_6a_)	
	Apex of antitragus (AT_1, 2, 4i_)	

### Acupuncture plus auricular acupressure treatment group

All acupoints are punctured by filiform needles when patients are lying in a comfortable supine position. Sterile, disposable Hwato needles (provided by Suzhou Hwato Medical Instruments Co. Ltd, Suzhou, China) are used in this study; they are 25 to 50 mm in length and 0.30 mm in diameter. The needle is inserted with the double hand-needle insertion technique. The depth of insertion is adjusted based on the standard permissible depth of insertion for each acupoint. The needle is then twirled, rotated, lifted and thrust moderately until achieving De qi sensation. The needles are retained for 30 minutes in every session and manipulated twice every 10 minutes with intermittent stimulation. Each manipulation lasts for 10 seconds. All needles are taken out with clean cotton balls to avoid bleeding after 30 minutes. Every patient will receive 28 sessions of acupuncture in total over a period of 12 weeks: three sessions per week in the first 4 weeks, every 2 days with a 1-day interval; and two sessions per week in the following 8 weeks, every 3 days with a 2-day interval.

All of the auricular points will use plaster therapy. One piece of Semen Vaccariae is put in the middle of one piece of 0.5 cm × 0.5 cm medical adhesive plaster. After sterilizing the skin of the auricular points, the plasters are stuck to the points with hemostatic forceps. The patients are required to press the auricular points gently by themselves three to five times a day lasting 1 minute, especially pressing them half an hour before sleep for 2 minutes, until the patients have distention, soreness, numbness, and warm sensation with the local auricular skin congestive, flashed and hot. The strength of pressing should consist of the individual’s endurance. The plaster with Semen Vaccariae is exchanged for a fresh set twice weekly for 12 consecutive weeks, every 3 days with a 2-day interval, both ears used alternately.

### Climen® control group

The patients are prescribed Climen® (complex packing estradiol valerate with cyroterone acetate tablets; Bayer Healthcare Company Limited) for three cycles: a 28-day sequential therapy combing estradiol valerate 2 mg/day (white tablets) from day 1 to day 11, and estradiol valerate 2 mg/day plus cyroterone acetate 1 mg/day (pink tablets) from day 12 to day 21, followed by a 7-day treatment-free interval.

### Outcome measurement

The primary outcome of this trial is the MRS, which is widely used for evaluating the severity of aging symptoms. Eleven questions of the MRS can be classified into three categories: psychological, somatic, and urogenital. A higher score indicates worse symptoms. The primary outcome is measured at randomization and another five points (4, 12, 16, 24, and 36 weeks after randomization). The secondary outcomes include the following items: Menopause-Specific Quality of Life; average hot-flash score during 24 hours; and the level of estradiol, follicle-stimulating hormone, and luteinizing hormone in serum. The first two secondary outcomes are measured at randomization and 4, 12, 16, 24, and 36 weeks after randomization. The other secondary outcomes are measured before randomization and 12 and 24 weeks after randomization.

All patients are asked to fill in a 7-day hot flash diary before randomization and 4, 12, 16, 24, and 36 weeks after randomization. After treatment, patients will be encouraged to finish these diaries by short messages, telephone calls, and emails in order to avoid selective loss to follow-up.

To exclude patients who have serious heart, liver, and kidney diseases, all participants will also receive routine tests of blood, liver function, kidney function, and electrocardiogram before randomization. Patients will also receive breast ultrasound and gynecological B ultrasound to exclude some uncovered galactophore and gynecological diseases. Meanwhile, aiming to evaluate the side effects of both methods, participates will receive the following items after the end of treatment: breast ultrasound and gynecological B ultrasound; and liver function (alanine aminotransferase, aspartate aminotransferase) and kidney function (blood urea nitrogen, serum creatinine).

This study will also estimate the expectations of participants using the credibility and expectancy questionnaire, aiming to clarify whether expectations make an impact on outcomes.

All patients in this study are required to document whether or not they take other medicine to relieve their perimenopause-related symptoms during 36 weeks, including the name and dosage of the medicine, the time and duration of taking, the reasons and the side effects of the medicine.

During the trial, all adverse events are to be recorded during treatment and the follow-up period, including bleeding, hematoma, fainting, serious pain, local infection, and so on, caused by acupuncture; and irregular vaginal bleeding, breast tenderness, headaches, nausea, and so on, caused by Climen®. Serious adverse events associated with the trial should be reported to the principal investigator immediately. All details will be documented, treatment options for rescue will be given at once, and appropriate action will be taken to prevent recurrence.

All acupuncturists were qualified to perform this trial after they participated in special training classes and passed the examination. The special training classes were held twice in August 2013, aiming to make all of the acupuncturists well understand all details of this trial. For instance, they were trained to use the central randomization method, to fill in the case report form, to find the correct points, to manipulate the needles, and so on. Additionally, to ensure the quality of this trial, the clinical monitors will check the processes of the trial and document the details of the processes once a month in every hospital. Moreover, monitors named by the principle investigator will check the accuracy and validity of the original data from the clinical centers. Regular meetings will be held to consider the recruitment rate, adverse events, protocol violations, difficulties and problems appearing during this study, and so on.

Patient drop-outs, their reasons, and their compliance will be recorded at the 36th week after randomization. All patients will be recorded until the end of this trial.

### Statistical analysis

All data from this study will be analyzed by special analysts with SPSS 20.0 (IBM Corp., Armonk, NY, USA).

The tests of outcomes are based on the intention-to-treat population. Sensitivity analyses are performed for the primary outcomes (MRS measured 16 weeks after randomization) by replacing missing data with multiple imputations and lost observations carried forward using SPSS 20.0. Multiple imputations are calculated using the propensity score method. The MRS is used as a dependent variable in an analysis of covariance, with the groups as random factors, and with baseline MRS and age as covariates, to account for potential baseline differences. Adjusted mean treatment effects are given alongside corresponding 95% confidence intervals and *P* values. The same analysis method will be performed for all secondary outcomes.

In addition to the above analysis, we will perform an exploratory analysis to describe group means over time. We will calculate summary statistics to reveal whether the two groups are changing in a similar or different fashion. A two-sided test is applied for available data, and *P* < 0.05 is considered statistically significant.

There is one acupuncturist in each center to do all treatment, which probably introduces a clustering effect in this trial. We therefore calculated the intracluster correlation coefficient from the result of this trial and report the coefficient [28].

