**Figure 1 F1:**
[figure not shown]
**Trial flow chart.** CPA, cyroterone acetate; E_2_V, estradiol valerate. Climen® from Bayer Healthcare Company Limited (Guangzhou, China).

**Table 1 T1:** Trial processes chart

	**Baseline**	**Treatment phase**			**Follow-up phase**		
	**Week −1**	**Week 0**	**Week 4**	**Week 12**	**Week 16**	**Week 24**	**Week 36**
Patients							
Enrollment	×						
Informed consent	×						
Signed informed consent		×					
Medical history	×						
Physical examination	×		×	×			
Laboratory test	×			×		×	
Breast and gynecological ultrasound	×			×			
Randomization		×					
Expectation of acupuncture		×					
Intervention							
Acupuncture plus auricular acupressure treatment group (*n* = 103)			28 sessions of acupuncture				
Comparison							
Climen® control group (*n* = 103)			E_2_V 2 mg/day for days 1 to 11 and E_2_V 2 mg + CPA 1 mg/day for days 12 to 21				
Outcomes							
MRS		×	×	×	×	×	×
MENQOL		×	×	×	×	×	×
Average hot flash score during 24 hours		×	×	×	×	×	×
Serum estradiol, FSH and LH levels	×			×		×	
Patients’ satisfaction			×	×			
Trial evaluation							
Safety of acupuncture			×	×			
Cost–benefit analysis				×			
Reasons of drop-outs or withdrawals							×
Patients’ compliance							×
Adverse events							×
Medicine alliance							×

CPA, cyroterone acetate; E_2_V, estradiol valerate; FSH, follicle-stimulating hormone; LH, luteinizing hormone; MRS, Menopause Rating Scale; MENQOL, Menopause-Specific Quality of Life. Climen® from Bayer Healthcare Company Limited (Guangzhou, China).

These participants will be randomly assigned to two groups (AA treatment group and Climen® control group) through central randomization in a 1:1 ratio. The central randomization system will be used and performed by the Clinical Evaluation Center of China Academy of Chinese Medical Sciences in Beijing. Authorized researchers can obtain random numbers and group assignments by calling the central randomization service number or logging into the website to apply. This procedure assures that randomization will not be influenced either by the acupuncturist or the patients.

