### Patients

#### Study population and sample size

This study focuses on women experiencing perimenopausal syndrome. According to the previous study by Guang’anmen Hospital, China Academy of Chinese Medical Sciences (results still unpublished), the improvement of Menopause Rating Scale (MRS) scores of the electro-acupuncture group and the sham acupuncture group were 6.5 and 2, respectively. The difference in scores between the two groups was 4.5, and electro-acupuncture was not superior to sham acupuncture. Accordingly, we assume that a difference within 4.5 indicates acupuncture is not inferior to Climen® treatment. Using a non-inferiority design, and assuming a power of 90%, an alpha value of 5%, and a population standard deviation of 10, a total of 206 patients will be needed in this study. Each group needs 103 patients (assuming a 20% dropout rate).

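### Non-inferiority is tested on the ITT population with no stated check for non-adherence or other medicines, and compliance is scheduled for recording at week 36

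*Protocol article*

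**What the plan says.** Under Study population and sample size, the protocol article adopts a non-inferiority design: "we assume that a difference within 4.5 indicates acupuncture is not inferior to Climen® treatment". The planning values are given as "assuming a power of 90%, an alpha value of 5%, and a population standard deviation of 10", with a 20% allowance for dropout, and "a total of 206 patients will be needed in this study".

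Under Statistical analysis, the analysis set is named: "The tests of outcomes are based on the intention-to-treat population". The primary outcome is identified there as MRS at week 16. Its sensitivity analyses are multiple imputation and carry-forward. The article names no per-protocol or as-treated set.

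Under Outcome measurement, the timing of adherence data is given: "Patient drop-outs, their reasons, and their compliance will be recorded at the 36th week after randomization". Table 1 agrees, marking these rows in the week 36 column and nowhere else. The same section requires patients to document "whether or not they take other medicine to relieve their perimenopause-related symptoms during 36 weeks", with name, dosage, timing, duration and reasons. No stated analysis uses that record.

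**The concern.** In a superiority trial, departures from assigned treatment usually make ITT cautious. In a non-inferiority trial, anything that shrinks a real difference between the arms helps the claim. Two departures have that effect here if Climen is truly better: women stopping their tablets, and women in the acupuncture arm taking other medicine that relieves symptoms. Both are foreseeable. The Background says women turn away from HRT because of its risks, the Discussions section concedes that patients are difficult to blind, and the sample size already assumes 20% dropout.

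The two listed sensitivity analyses vary how missing scores are filled in. Neither asks whether the result would hold among women who took the treatment they were assigned. A conclusion that acupuncture is not inferior to HRT could therefore owe something to poor adherence or added medicine, and no stated analysis would show it. If compliance is first written down at week 36, it is recalled 24 weeks after the 12-week treatment ended and 20 weeks after the primary time point, and some drop-outs will no longer be reachable.

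**Working it through.** **Inputs from the article.** Margin 4.5, SD 10, power 90%, alpha 5% (sidedness not stated for the sample size), 103 per arm, 20% dropout, week-16 primary time point, 95% confidence intervals.

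**The plan's own figure.** Per arm, n = 2 × [SD × (z_alpha + z_power) / margin]², with the true difference taken as 0 (an assumption; the article does not state it).

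- One-sided 5%: 2 × [10 × (1.645 + 1.282) / 4.5]² = 84.6, so 85. Then 85 × 1.2 = 102 per arm, total 204. With the t distribution, 86 × 1.2 = 103.2. Either is close to 103 per arm and 206 in total.
- One-sided 2.5%: 2 × [10 × (1.960 + 1.282) / 4.5]² = 103.8, so 104 per arm, total 208. This comes close to 206 only without a dropout allowance.

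The stated 206 is reproduced and is not disputed here.

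**Illustration of dilution.** Assumptions: the true difference among adherent women equals the margin (4.5 in favour of Climen), and a share f of women contributes no between-arm contrast. The documents give no adherence rate, so f is assumed and shown as a range. With 20% dropout, 103 × 0.8 = 82 are analysed per arm, and SE = 10 × √(2/82) = 1.5617. The chance that the upper limit of a two-sided 95% interval falls below 4.5 is Φ[(4.5 − 4.5(1 − f)) / 1.5617 − 1.96].

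| f | Observed difference expected | False non-inferiority |
|---|---|---|
| 0% | 4.50 | 2.5% |
| 10% | 4.05 | Φ(0.288 − 1.96) = 4.7% |
| 15% | 3.825 | Φ(0.432 − 1.96) = 6.3% |
| 20% | 3.60 | Φ(0.576 − 1.96) = 8.3% |

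If outcomes are available or imputed for all 103 per arm and the full-data SE is used, SE = 10 × √(2/103) = 1.393, and the values at f = 10% and 20% are 5.1% and 9.4%. At a nominal one-sided 5%, the values at f = 10% and 20% are 8.7% and 14.3% with 82 per arm, and 9.3% and 15.9% with 103 per arm.

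**The opposite direction.** If departures widen the difference by the same amounts (missed acupuncture, or other medicine in the Climen arm), the expected differences are 4.95 and 5.40. The chance of claiming non-inferiority then falls to Φ(−0.288 − 1.96) = 1.2% and Φ(−0.576 − 1.96) = 0.6%. The net direction depends on which arm departs and how.

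**Power of a per-protocol set** (true difference 0, one-sided 2.5%): 82.2% with 82 per arm, 77.6% with 73 and 72.8% with 65. The last two sizes correspond to excluding a further 10% and 20% of the 82.

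**Timing of records.** Table 1 also marks adverse events at week 36 only, although Outcome measurement has them recorded throughout treatment and follow-up. The week 36 mark may therefore mean collation at study end. The article does not say which meaning applies to compliance and drop-out reasons.

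**The case against.** Five points can be made for the plan.

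- **Direction.** A reader might infer that any departure in either arm makes the arms look alike. It does not. Missed acupuncture, if acupuncture has any effect, and other medicine in the Climen arm both tend to widen a difference in favour of Climen. This stands, and it limits the point to a risk that depends on which arm departs.
- **Feasibility.** A reader might infer from the week 36 entry that no credible per-protocol set could be built. The article does not support that. Other medicines are documented with timing over the whole 36 weeks, sessions are delivered by one acupuncturist per centre so attendance can be seen at source, monitors document trial processes monthly, and the week 36 mark may be collation. What stands is that the stated timing does not assure reliable adherence data, tablet-taking above all.
- **Pragmatic aim.** The Discussions section calls the trial pragmatic, for which ITT is a defensible primary set. This stands, and ITT should remain primary.
- **Co-primary test.** A reader might go further and require non-inferiority in both sets. A per-protocol set conditions on behaviour after randomization, measured by tablets in one arm and sessions in the other, among unblinded patients. Requiring both sets would also cap power at about 82% or less at one-sided 2.5%, against the planned 90%. The documents do not compel that price.
- **Unseen documents.** A supportive set could be defined in an SAP or full protocol not shown. That is possible. But the article itself fixes the analysis set and lists the sensitivity analyses, and that list does not match the non-inferiority aim.

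**Conclusion.** The point holds as a moderate one that should be addressed. The stated tests rest on ITT, the stated sensitivity analyses deal only with missing data, and nothing stated examines whether non-adherence or other medicines contributed to a non-inferiority result. The rise from 2.5% to between 4.7% and 8.3% shows how large the effect could be. It rests on a true difference exactly at the margin, SD 10, 82 analysed per arm, and an assumed 10% to 20% of women contributing no contrast, all acting in one direction. It is not an estimate of what will happen, and offsetting departures could cancel or reverse it.

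The week 36 timing is a secondary weakness. It makes adherence data less reliable if it means first recording, and is only unclear wording if it means collation. The article does not show that a per-protocol analysis would be impossible, or that ITT is the wrong primary set.

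**What to change.** 1. Keep ITT as the primary analysis. Add a pre-specified supportive per-protocol analysis of week-16 MRS against the same 4.5-point margin.
2. Define the per-protocol set before anyone sees outcomes by group, using tablets taken or sessions attended and the record of other medicines already kept.
3. Report whether the two analyses agree, and interpret a non-inferiority claim cautiously if they do not.
4. In Table 1 and Outcome measurement, record compliance at the existing week 4 and week 12 visits and drop-out reasons when they occur. If week 36 means collation, say so.

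The cost is one extra analysis, which carries its own selection bias and, as supportive evidence, has less power than planned for the trial, plus earlier completion of existing records. No new visits are needed. The trial is recruiting, and adherence not captured at the time is hard to reconstruct, so the change in recording is best made soon.

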**Design:**

A multicenter randomized controlled trial with two parallel arms is underway in China. Two hundred and six women with perimenopausal syndrome will be randomly assigned to a treatment group using acupuncture plus auricular acupressure (AA group) and a control group using Climen® (Bayer Healthcare Company Limited, Guangzhou, China), a 28-day sequential hormone replacement therapy, in a 1:1 ratio. Participants in the AA group will receive three acupuncture sessions per week in the first 4 weeks and two sessions per week in the following 8 weeks, for a total of 28 sessions over 12 weeks. Auricular points will be plastered by Semen Vaccariae twice per week for a consecutive 12 weeks, with both ears used alternately. The Climen® control group is prescribed a tablet containing estradiol valerate 2 mg/day for the first 11 days, and a tablet containing estradiol valerate 2 mg/day plus cyroterone acetate 1 mg/day for the following 10 days. The total treatment period of the control group is three cycles. The post-treatment follow-up period will last 24 weeks. The primary outcome is the Menopause Rating Scale (MRS) assessed at baseline and 4, 12, 16, 24 and 36 weeks after randomization. The secondary outcomes are Menopause-Specific Quality of Life, average hot flash score during 24 hours, serum estradiol, follicle-stimulating hormone and luteinizing hormone level. The first two secondary outcomes are measured at the same point as the MRS. Other secondary outcomes are measured at baseline and 12, 24 weeks after randomization.

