The total observation period within this study is 37 weeks, including 1 week of baseline, 12 weeks of treatment and 24 weeks of follow-up. After randomization, participants will receive 28 sessions of acupuncture over a period of 12 weeks plus auricular acupressure or take Climen® (from Bayer Healthcare Company Limited, Guangzhou, China) tablets for three cycles. Acupuncture will be given as three sessions weekly in the first 4 weeks and two sessions weekly in the following 8 weeks for each patient. Each session will last 30 minutes. The follow-up period will last 24 weeks (13 to 36 weeks after randomization). Patients will be assessed before randomization as well as 4, 12, 16, 24 and 36 weeks after randomization.

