HRT has been in use for more than half a century and is regarded as a gold standard treatment for vasomotor, urogenital symptoms and their potential consequences such as sleep problems, and mood disorders [31-33]. HRT can improve the health-related quality of life through the alleviation of these symptoms. Meanwhile, HRT is beneficial to prevent aging women from osteoporosis, metabolic syndrome, and cardiovascular problems [4]. HRT is thus an ideal treatment for females with perimenopausal syndrome. Given all patients in this trial have an intact uterus, we choose estrogen plus progestin therapy to negate the risk of endometrial cancer rather than using estrogen alone, and 12-week treatment for women aged 40 to 55 should be safe according to the statement of the North American Menopause Society [4]. Furthermore, studies have shown that sequential estradiol valerate and cyroterone acetate combinations: relieve climacteric complaints via increasing serum estrogen, and provide a good menstrual cycle inducing a physiological secretory transformation of the endometrium without side effects [34]; exert a positive effect on body fat mass and distribution [35]; and may have protective effects for postmenopausal bone loss [36]. We therefore chose Climen® as a positive drug control.

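### The primary MRS time point is fixed only in a parenthesis, at week 16, when both treatments have ended, so non-inferiority there is not a comparison with HRT in use

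*Protocol article*

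**What the plan says.** Three parts of the protocol article describe when the primary outcome is measured.

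- Abstract, Design: "The primary outcome is the Menopause Rating Scale (MRS) assessed at baseline and 4, 12, 16, 24 and 36 weeks after randomization".
- Outcome measurement: "The primary outcome is measured at randomization and another five points (4, 12, 16, 24, and 36 weeks after randomization".
- Statistical analysis: "Sensitivity analyses are performed for the primary outcomes (MRS measured 16 weeks after randomization".

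The first two choose no visit. The third names week 16, in a parenthesis within a sentence about missing data.

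The schedule comes from two places. The Climen® control group section prescribes the drug "for three cycles: a 28-day sequential therapy combing estradiol valerate 2 mg/day (white tablets) from day 1 to day 11", then the second tablet ("pink tablets) from day 12 to day 21, followed by a 7-day treatment-free interval"). Study design gives 12 weeks of treatment in both arms and then states: "The follow-up period will last 24 weeks (13 to 36 weeks after randomization".

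The comparison is framed as non-inferiority. Background gives the aim as judging acupuncture against HRT. Study population and sample size treats a difference within 4.5 MRS points as not inferior to Climen treatment, without attaching that margin to a visit.

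**The concern.** There are two linked problems. First, with five candidate visits and one parenthetical choice, the visit that carries the main conclusion is not securely fixed.

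Second, the visit that is named falls when neither treatment is being given. A non-inferiority conclusion relies on the reference treatment having its effect when the comparison is made. The Discussions section justifies the control on that ground ("HRT has been in use for more than half a century and is regarded as a gold standard treatment") and attributes relief of complaints with this drug combination to raised serum estrogen. Once tablets stop, that effect may wane. If it does, and AA does not lose clearly more, a real on-treatment deficit is partly hidden by week 16. The trial could then report AA as not inferior to HRT although it was worse by the full margin while HRT was being taken.

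**Working it through.** **Inputs from the article.** Three 28-day cycles with tablets on days 1 to 21; AA for 12 weeks; margin 4.5; SD 10; 103 per group; 20% dropout; 95% confidence intervals and two-sided tests.

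**The plan's own sample size.** With one-sided alpha 5% and 90% power, n per arm = 2 × [10 × (1.645 + 1.282) / 4.5]² = 84.6, so 85. Multiplying by 1.2 gives 102 per arm, 204 in total, close to the stated 206. The formula contains no time point, so changing the primary visit leaves N unchanged.

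**Timing, assuming tablets start at randomization.**

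- Last scheduled tablet: 2 × 28 + 21 = day 77.
- Week 16: 16 × 7 = day 112, which is 112 − 77 = 35 days after the last tablet.
- End of AA: about day 84, so week 16 is about 112 − 84 = 28 days later.
- Week 12: day 84, which is 84 − 77 = 7 days after the last tablet, at the end of the final tablet-free interval.

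A later tablet start would shorten the two tablet gaps.

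**Illustration of size.** Evaluable per arm: 80% of 103, about 82. SE = 10 × √(2/82) = 1.56. The 95% interval corresponds to one-sided 2.5%. For a true week-16 deficit D,

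P(non-inferior) = Φ((4.5 − D)/1.56 − 1.96).

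Assume that AA is truly 4.5 points worse than Climen on treatment, exactly at the margin. With no fading, D = 4.5 and the probability is 2.5%.

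Scenario A: both effects fade by the same fraction f, so D = 4.5 × (1 − f). Scenario B: AA keeps its full effect and Climen loses a fraction f of an assumed 6.5-point effect, so D = 4.5 − 6.5f.

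| f | A: D | A: false non-inferiority | B: D | B: false non-inferiority |
|---|---|---|---|---|
| 25% | 3.375 | 10.8% | 2.875 | 17.9% |
| 50% | 2.25 | 30.2% | 1.25 | 54.8% |
| 75% | 1.125 | 58.0% | −0.375 | 87.7% |

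At one-sided 5%, scenario A gives 17.8%, 41.9% and 69.7% against a nominal 5%.

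The 6.5 in scenario B is an assumption. The article reports that figure only as the improvement in the electro-acupuncture arm of an unpublished study, and it gives no Climen effect on the MRS. Scenario A does not need it.

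**When the direction reverses.** The deficit grows only if AA loses more points than Climen. With the assumed 6.5, AA's on-treatment effect is 6.5 − 4.5 = 2.0. If AA lost all 2.0 points while Climen lost 25% (1.625), D = 4.5 − 1.625 + 2.0 = 4.875, and the probability is Φ(−0.375/1.56 − 1.96), about 1.4%, below nominal.

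**The case against.** A reader might infer that AA is being compared with withdrawn HRT while AA itself continues. The article does not support that: acupuncture and auricular plasters also end at 12 weeks, so both arms are off treatment at week 16. This stands, and it makes scenario B the more extreme of the two. It does not remove the problem, because equal proportional fading still shrinks a deficit.

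A reader might also infer that bias toward non-inferiority is established and large. The article gives neither a rate at which relief fades nor a Climen effect on the MRS, so the direction is conditional and the size cannot be derived. On direction, the only evidence in the article is a study cited in Discussions, where acupuncture was superior to HRT during six months of follow-up. That favours AA after treatment but gives no figure for week 16.

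Nor is a non-inferiority test at week 16 spelled out. The Statistical analysis section describes an analysis of covariance with two-sided tests, and the margin is tied to no visit. Putting the two together is an inference, although it is the only reading in which the named primary visit and the stated design meet.

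Finally, durability is a declared interest: the trial is called pragmatic, and Discussions wants the continuing effect of acupuncture compared with the drug. A post-course comparison may be deliberate. That is a good reason to keep week 16 in the plan, but it does not support a claim about HRT in use, and the article gives no reason for making week 16 primary.

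**Conclusion.** The concern holds in this form: the primary time point is poorly fixed, and the only visit named is an off-treatment one that does not match the stated aim of non-inferiority to Climen treatment. The 35-day and four-week gaps follow from the article's schedule, given a tablet start at randomization. A shift toward non-inferiority is expected unless AA loses clearly more benefit than Climen after stopping, and nothing in the article suggests that it does.

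The probabilities are illustrations that rest on a true deficit of 4.5, SD 10, 82 evaluable per arm and assumed fading. For losses of 25% to 75% they run from about 11% to 58% with equal fading, and from about 18% to 88% if AA persists fully, against a nominal 2.5%. They would be lower if AA faded faster. The case for correction rests on the mismatch between visit and claim, and does not depend on any one of these figures.

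**What to change.** Before any comparative data are seen, name the end-of-treatment (week 12) MRS as the single primary non-inferiority time point, tie the 4.5-point margin to it, and state this identically in the abstract, Outcome measurement and Statistical analysis. Keep week 16 as a key secondary comparison of persistence after treatment. Make no claim of non-inferiority to HRT in use from weeks 16 to 36.

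The cost is wording in the protocol and the registration. Table 1 already schedules the MRS at week 12, the sample size does not change, and Trial status says that recruitment is still under way.

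There are two downsides. Week 16 loses its primary status. Week 12 (day 84) falls at the end of the last 7-day tablet-free interval, just as AA finishes, so a smaller version of the same issue remains and should be acknowledged when the result is interpreted.
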